### Low fat

A low fat diet containing (25% of energy from fat) with a higher carbohydrate intake (55% of energy) with complex carbohydrate sources encouraged and a moderate protein intake (20% of energy). This dietary approach recommends low fat foods and snacks and increases fruit and vegetable intake.

### Control group

The control group will be offered treatment for 24 weeks after the formal control period (of 12 weeks).

### Physical activity and sedentary behaviours

The intervention groups will receive the Australian National Health and Medical Research Councils 'Get out and get active' booklet. Emphasis will be placed on a reduction in sedentary behaviours. Activity will be measured by qualitative comparison of the measures from The Adolescent Physical Activity Recall Questionnaire [40] and a 4 day physical activity diary which will be completed at M1 and M2 (all groups).

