In our feasibility study we found that the adolescents referred for weight loss were exceptionally sedentary with activity diaries showing a mean of 10.3 hours/day of seated activity including 4.4 hours of screen time [19]. The physical activity advice provided in the feasibility study was based on the age appropriate Australian Physical Activity Recommendations, which suggests a minimum of 60 minutes per day of moderate and vigorous physical activities [20,21]. Our experience was that young people participating in the feasibility study were reluctant to increase their activity levels based on activity diaries completed over the study period [19]. Therefore, we aim to provide advice that concentrates on a reduction in sedentary behaviour across all groups. Sedentary behaviours will be measured by a physical activity diary and a questionnaire pre- and post intervention to monitor compliance with this strategy.

There is increasing recognition of the need for psychological adjuncts to behavioural approaches in any intervention for childhood weight management [22]. Obesity during childhood and adolescence is associated with negative social and psychological sequelae during a developmentally sensitive period. Overweight children have been found to be at higher risk of low self esteem and low self worth, along with lower levels of perceived competence and social acceptance, compared with healthy weight children [23]. Obese young people are also more likely to be socially isolated and peripheral to social networks than their normal weight peers [24]. Adolescence represents a high risk period for obese youth to experience peer victimisation, such as bullying and teasing due to their weight [25]. In our feasibility study (n = 30) 67% of parents reported that one of the reasons for seeking weight management advice was that their child endured significant teasing/bullying at school, had few friends or difficulty in making friends. Two were refusing to attend regular school reportedly due to weight related victimisation [17]. Evidence also exists that overweight children suffer the psychological distress of early discrimination which may influence their socioeconomic attainment later in life [26].

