### Diet and activity

Participants will be asked to complete a 4 day food and activity records at M1 and M2. Food records will be analysed using a standard nutrient analysis package (FoodWorks). Physical activity habits will be assessed using the diary and the Adolescent Physical Activity Recall Questionnaire [40].

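### Adherence to the sedentary-behaviour advice is to be judged by a qualitative comparison of instruments that yield numbers, so the plan promises no estimate or interval for it by group

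*Protocol article*

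**What the plan says.** The Background explains that feasibility participants were reluctant to become more active, so the trial will concentrate on sitting less. It then gives the purpose of the measurements: "Sedentary behaviours will be measured by a physical activity diary and a questionnaire pre- and post intervention to monitor compliance with this strategy".

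The method is in the section Physical activity and sedentary behaviours: "Activity will be measured by qualitative comparison of the measures from The Adolescent Physical Activity Recall Questionnaire" together with "a 4 day physical activity diary which will be completed at M1 and M2 (all groups").

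The Diet and activity section describes the same two instruments without the qualifier: "Physical activity habits will be assessed using the diary and the Adolescent Physical Activity Recall Questionnaire".

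Elsewhere the article uses such diaries numerically. The Background reports feasibility "activity diaries showing a mean of 10.3 hours/day of seated activity including 4.4 hours of screen time". The Energy prescription section derives a physical activity level (PAL) from a 4-day activity diary and uses it to set each participant's energy target. The Statistical Analysis Plan section of the article names no analysis of activity, and activity is not among its candidate covariates.

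**The concern.** Whether participants followed advice to sit less is a question of quantity: how many hours, before and after, in each group. A qualitative comparison does not answer it. It produces no mean change, no between-group difference and no interval.

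This is more than detail left to a document that is not shown. The article does state a method, and that method does not fit the purpose the article itself gives for the data.

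At stake is the account of a co-intervention delivered with both diets. The article wants to learn about macronutrient composition. A reader who sees a difference in BMI z-score between diets will ask whether the groups also changed their sitting and screen time to different degrees. Under the stated method the report would answer with an impression, although the data needed for an estimate will have been collected.

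**Working it through.** **Step 1. Purpose, data and method set side by side.**

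| Item | Where | What it gives |
|---|---|---|
| Purpose | Background | monitor compliance with the sedentary-behaviour advice, before and after |
| Timing and groups | Physical activity and sedentary behaviours | M1 and M2, all groups |
| Diary output in the feasibility study | Background | 10.3 h/day seated, of which 4.4 h screen time |
| Diary output in the trial | Energy prescription | a numerical PAL |
| Method | Physical activity and sedentary behaviours | qualitative comparison |
| Method, second description | Diet and activity | assessed using both instruments, no qualifier |

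Purpose and data are quantitative. Only the stated method is not.

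**Step 2. Does another reading of the sentence remove the problem?** It could mean comparing the questionnaire with the diary, and not comparing groups or time points. On that reading the section states no assessment of change or of group differences, so the compliance purpose is still unmet. Either reading needs correcting.

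**Step 3. Does it touch the primary comparison?** The Sample size section names change in BMI z-score, low fat versus reduced carbohydrate, as primary. Its inputs are a difference of 0.09, SD 0.12, two-sided α = 0.05 and power 80%.

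- Standardised difference: 0.09 / 0.12 = 0.75.
- Normal approximation: n = 2 × (1.960 + 0.842)² / 0.75² = 27.9, so 28 per arm.
- t-test version: 28.9, so 29 per arm, with power 0.801 at 29.

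The stated 29 is reproduced. No activity measure enters it, so the way activity is summarised changes neither the sample size nor the power.

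**Step 4. What a quantitative comparison could show.**

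- Diet versus diet, 29 completers each: 80% power at d = 0.749.
- Half-width of the 95% interval for the difference: 2.003 × √(2/29) = 2.003 × 0.2626 = 0.53 SD.

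The documents give no SD for change in seated time. For a range of assumed values:

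| Assumed SD of change (h/day) | Difference with 80% power (0.749 × SD) | 95% half-width (0.526 × SD) |
|---|---|---|
| 1.5 | 1.12 | 0.79 |
| 2 | 1.50 | 1.05 |
| 3 | 2.25 | 1.58 |

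For scale, the feasibility mean was 10.3 h/day seated. Against the control group (12 completers) precision is lower. The protocol's inputs give a detectable difference of 0.1183 at SD 0.12 for 12 versus 29, which is 0.1183 / 0.12 = 0.99 SD.

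**The case against.** The strongest counter-argument starts from a conclusion that a reader might draw: that the trial could not tell whether a BMI z-score difference between the diets came from activity instead of diet. The documents do not support this.

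- The diet arms are randomised, by weighted minimisation on gender and Tanner stage (Allocation to groups).
- As described, both receive the same booklet and the same emphasis on sitting less, and a standardised manual with pre-set session outlines is meant to keep delivery alike (Interventions).
- Activity after randomisation is therefore a possible mediator or an adherence measure, not a confounder. The estimated effect of assignment to one diet programme or the other stays valid however activity is summarised.
- A table of activity differences could not separate diet from activity in any case. That needs mediation assumptions.

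All of this stands.

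It can also be said that activity is neither a listed outcome nor a hypothesis, that the numbers are still collected, that nothing forbids a quantitative summary, and that tabulation of a process measure is often left to a fuller document. This stands in part. The defect lies in the stated analysis, not in the data, and it is small. But the article did not leave the method open. It named one that does not serve its own purpose.

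A related point concerns diet versus control. The Background says "we aim to provide advice that concentrates on a reduction in sedentary behaviour across all groups", while the later section says "The intervention groups will receive the Australian National Health and Medical Research Councils 'Get out and get active' booklet". What the control group receives during its 12 weeks is thus unclear, and these passages should be reconciled. A numerical summary by group would also help readers there.

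**Conclusion.** The point holds as a limited, nearly free improvement to the plan. The stated qualitative comparison does not fit instruments that yield numbers and are meant to monitor compliance, and as written it gives no estimate or interval for adherence by group. The effect is confined to the description of adherence and to how firmly a diet-versus-diet result can be interpreted in macronutrient terms. There is no bias in the randomised comparison of BMI z-score and no effect on its sample size or power.

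The gain from the change is also limited. With 29 completers per diet, a difference must be about 0.75 SD to have 80% power, and the 95% interval extends about 0.53 SD either side of the estimate. Absence of a detected difference should not be read as equal activity.

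This rests on two assumptions. The trial diary is taken to record seated and screen time as the feasibility diaries did. The hours/day figures depend on assumed SDs of 1.5 to 3, which the documents do not supply.

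**What to change.** In Physical activity and sedentary behaviours, replace the qualitative comparison with the following:

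- Change from M1 to M2 in diary seated hours/day, diary screen hours/day and questionnaire activity is reported by randomised group, among participants with data at both points and with their number shown.
- Between-group differences are given with 95% confidence intervals.
- These are labelled descriptive adherence measures. The primary analysis is not adjusted for them, and no claim is made that they separate diet effects from activity effects.
- An interval that includes zero is not reported as evidence that activity was the same.

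Bring the wording in Diet and activity into line. The instruments are already completed by all groups at M1 and M2, so no new data are needed. The cost is some diary coding and one extra table.

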### Assessments and Measurement instruments

The laboratory technician conducting body composition measurements will be blinded to group allocation. The following assessments will be completed at M1 and M2 unless otherwise stated (see figure 1).

### Anthropometry and body composition

These measurements will be undertaken by the body composition laboratory technician using standard operating procedures. Height, weight, waist and hip circumferences will be measured. BMI z-score will be calculated by the LMS method [41] using CDC reference data. Body composition will be assessed by 3 methods: air displacement plethysmography (BodPod™), total body potassium (TBK) and bioelectrical impedance (Bodystat 1500MDD). These measures are non-invasive and we have validated these for use in obese adolescents [42].

### Liver function and plasma lipid profiles

Fasting blood samples (10 ml) will be taken by trained phlebotomists at M1 and M2. Liver function tests (including total protein, albumin, total bilirubin, liver function enzymes (ALP, GGT, ALT and AST) and lipid profiles (including cholesterol fractions and triglycerides) will be measured using an automated Clinical Chemistry Analyser.

### Insulin resistance

Fasting glucose and insulin will be measured using an automated Clinical Chemistry Analyser. The homeostatic method will be used to calculate insulin resistance and beta cell function.

### Adipokines and inflammatory markers

Adipose tissue is not only a site of energy storage, but also an active endocrine organ secreting a number of hormones and cytokines that play critical roles in body energy homeostasis and metabolism [43]. We will measure the following adipokines and cytokines at M1 and M2: leptin, resistin, adiponectin, interleukin-6, TNFα, CRP, plasminogen activator inhibitor 1 (PAI1) and soluble ICAM-1 in plasma using a multiplexed immunoassay, analysed on the Luminex 100IS.

### Diet and activity

Participants will be asked to complete a 4 day food and activity records at M1 and M2. Food records will be analysed using a standard nutrient analysis package (FoodWorks). Physical activity habits will be assessed using the diary and the Adolescent Physical Activity Recall Questionnaire [40].

### Allocation to groups

Treatment allocation will depend on gender and Tanner Stage (pubertal stage). Weighted randomisation will be used so that the participants will be allocated to the treatment group that minimises the gender/Tanner Stage imbalance between groups with a probability of 0.8 and will be conducted by the study statistician ([name]). Participants will be informed as to which group they have been assigned at their baseline assessment and if they are in the active diet groups, an immediate appointment with a study dietitian will be made. The control group will be given an appointment to attend in 12 weeks time when they will be offered the intervention treatment of their choice.

### Compliance and retention strategies

Compliance to the dietary program will be monitored by the use of 4 day food dairies throughout the intervention and at each measurement point. To try and reduce attrition, volunteer families will have parking cost at the hospital paid and during the initial 12 week period there is frequent and intense therapist contact. In the feasibility study we documented a mean increase in plasma urea in the reduced carbohydrate group (not statistically significant) but it is suggestive that dietary protein shifts in the direction indicated by the food diaries. We will measure serum changes in urea and urates across groups over time and also measure serum vitamin B12 as a surrogate marker of protein intake as this has been shown to increase in adults on high protein diets [15]. We recognise this method has not been validated in children.

### Sample size

Our sample size calculations were based on our primary comparison, the difference in change in BMI z-score between the low fat and reduced carbohydrate groups. In our feasibility study (n = 30), the mean (SD) of BMI z-score changes over 12 weeks were -0.20 (0.17) and -0.11 (0.08) for the low fat and reduced carbohydrate groups respectively. In order to observe a clinically important difference in change of BMI z-score between the two intervention groups of 0.09, with α = 0.05 and power of 80%, and assuming standard deviation of 0.12, we require 29 individuals in each intervention group to complete the study. Assuming that 20% of participants will drop out of the study (in our feasibility study our attrition rate was 17%), we will enrol 35 individuals in each of the diet intervention groups. If 12 participants enrolled to the control group complete the 12 week wait-list period, we will be able to detect a difference of change in BMI z-score of 0.13 between the control group and either of the diet intervention groups (α = 0.05, power = 80%). If we assume 20% of control-group participants will drop out of the study, we will need to enrol 15 individuals in the control group.

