### Statistical Analysis Plan

Primary analysis will use the intention to treat principle, assuming return to baseline values for non-completers. Differences between participants who completed and withdrew will be assessed using t tests for continuous variables and Fisher's Exact Test for categorical variables. We shall examine weight loss over time using a mixed-effects model with a random intercept and slope for each participant. This method controls for the non-independence in results from the same participant and allows for heterogeneity between participants. Potential co-variates (gender, Tanner Stage, baseline weight) will be assessed, and, if appropriate, incorporated into the model. We will examine the effects of losses of body weight and body fat on clinically important markers of disease risk (lipids, blood pressure, waist: hip ratio, insulin resistance) using analysis of covariance. Data generated from the psychometric questionnaires (self-concept, anxiety, self-esteem and quality of life) will be used as secondary outcome variables to examine the extent and nature of psychological distress in obese adolescents pre-treatment and mixed-effects models will be used to examine changes in these parameters and their relationship with weight and waist: hip ratio change. Statistical significance will be based on two-tailed tests, with p < 0.05 considered significant.

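### The diet comparison's 80% power rests on an unexplained SD of 0.12; the feasibility SDs printed beside it imply about 0.133 and about 72% power, and the control figure fits an SD near 0.13

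*Protocol article*

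**What the plan says.** All the inputs stand in one paragraph, the Sample size section of the protocol article.

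- **Pilot data.** From a feasibility study of 30 participants it reports that "the mean (SD) of BMI z-score changes over 12 weeks were -0.20 (0.17) and -0.11 (0.08) for the low fat and reduced carbohydrate groups", in that order.
- **Target.** It aims at "a clinically important difference in change of BMI z-score between the two intervention groups of 0.09", "with α = 0.05 and power of 80"%.
- **SD and size.** It continues: "assuming standard deviation of 0.12, we require 29 individuals in each intervention group to complete the study". No source or reason for 0.12 is given.
- **Control comparison.** With 12 control completers, "we will be able to detect a difference of change in BMI z-score of 0.13 between the control group" and either diet group, again at alpha 0.05 and 80% power. No SD is restated for this figure.

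The Statistical Analysis Plan section fixes the sidedness: "Statistical significance will be based on two-tailed tests, with p < 0.05 considered significant".

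**The concern.** The paragraph carries the effect over from the feasibility study in full, since -0.11 minus -0.20 is 0.09, but not the spread. The SD it assumes lies below both the root-mean-square and the plain average of the two pilot SDs. An SD that is too small overstates power, and here it does so for the comparison that the section itself names as primary. The control sentence adds a doubt about consistency, because its 0.13 is larger than SD 0.12 would produce.

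At stake is the chance of missing the difference that the trial calls clinically important. The stated type II risk is 20%. With the pilot SDs it would be about 28%.

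**Working it through.** **Inputs.** Difference 0.09, SD 0.12, alpha 0.05, power 80%, 29 completers per diet arm, 12 control completers, and pilot SDs 0.17 and 0.08 (all from Sample size); two-sided testing (Statistical Analysis Plan); pilot diet choices of 10% unstructured low fat, 42% structured low fat and 48% reduced carbohydrate (Background).

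**Step 1: reproduce the plan's figure.** For a two-sample t test with n per arm, power is P(|T| > t(0.975; 2n-2)), where T is noncentral t with noncentrality (difference/SD) x sqrt(n/2). At SD 0.12 and n = 29 the noncentrality is 0.75 x sqrt(14.5) = 2.86 and power is 80.1%. Solving for 80% gives n = 28.9, so 29. The stated size follows from the stated inputs.

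**Step 2: the SD implied by the pilot.** With equal arms, the variance of the difference in means is (0.17² + 0.08²)/n. The equivalent common SD is sqrt((0.0289 + 0.0064)/2) = 0.133. This does not depend on how many pilot participants were on each diet. The plain average is (0.17 + 0.08)/2 = 0.125.

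If the pilot SDs are instead pooled by degrees of freedom, the pilot arm sizes matter, and the article does not give them. Taking them from the diet choices is an assumption:

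| Assumed pilot split (low fat v reduced carbohydrate) | Pooled SD |
|---|---|
| 13 v 14 or 13 v 15 (42% and 48% of 30) | 0.131 or 0.130 |
| 16 v 14 (unstructured low fat counted as low fat) | 0.136 |
| 11 v 19 (needed to reach 0.12 with all 30) | 0.120 |

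**Step 3: power for 0.09 with 29 per arm.**

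| SD | Power (t test) | Completers per arm for 80% | Difference detectable at 80%, n = 29 |
|---|---|---|---|
| 0.12 | 80.1% | 29 | 0.090 |
| 0.125 | 76.9% | 32 | 0.094 |
| 0.130 | 73.6% | 34 | 0.097 |
| 0.133 | 71.7% | 36 | 0.099 |
| 0.136 | 69.8% | 37 | 0.102 |

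A Welch test with SDs 0.17 and 0.08 gives 71.1% at 29 per arm.

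**Step 4: the control comparison.** With 29 v 12 completers (39 degrees of freedom) and two-sided alpha 0.05, the standardised difference detectable with 80% power is 0.986.

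- SD 0.12: 0.986 x 0.12 = 0.118 (0.115 by normal approximation).
- SD 0.130: 0.986 x 0.130 = 0.128.
- SD 0.133: 0.986 x 0.133 = 0.131.

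Working back, 0.13/0.986 = 0.132. Any value that rounds to 0.13 (0.125 to 0.135) needs an SD of about 0.127 to 0.137. Changing the diet arm does not rescue SD 0.12: 28 completers give 0.119 and 35 give 0.115.

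**The case against.** **It is an assumption, not a miscalculation.** This stands. The section says that it assumes 0.12 and does not claim that 0.12 is the pooled pilot SD, and 29 follows from it. The fault lies in the unexplained input.

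**The pilot cannot settle the SD.** This also stands. A reader might infer that the trial's real power is 70-74%. The document does not support that, because true power depends on a true SD that nobody knows. With 20 to 25 degrees of freedom, a chi-square 95% interval around a pooled SD of 0.13 runs from roughly 0.10 to 0.18 or 0.19, and 0.12 lies well inside it. The diet-choice percentages need not match the numbers analysed at 12 weeks, since pilot attrition was 17%. A split of 8 v 14 or 9 v 16 would give a pooled SD of 0.119 and about 80% power. Such splits are possible but undocumented. They also do not alter the 0.133, which follows from carrying the two SDs into equal arms.

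**The 0.13 can be reached with SD 0.12.** If alpha were split over the two control comparisons (0.025 each), SD 0.12 would give 0.131. So it cannot be said that 0.13 arises only from an SD near 0.13, or that a second SD was certainly used. But the sentence states alpha 0.05 and mentions no split, and at that alpha the figures disagree. It is also true that the 0.13 errs on the cautious side: with SD 0.12, power to detect it would be about 87%.

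**Covariates may reduce the residual SD.** They may, since the Statistical Analysis Plan section allows them if appropriate. The sample size paragraph does not rely on this.

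**No equivalence claim is planned.** Correct. The hypotheses are all of difference, so the possibility that a null result is read as showing the diets to be equal is a risk of interpretation, not a defect of the plan.

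**Conclusion.** The point holds conditionally. The article gives no basis for SD 0.12, and the data beside it point to about 0.133. If the feasibility SDs hold, 29 completers per diet arm give about 72% power for 0.09, or about 70-74% over plausible poolings, against the stated 80%. The same numbers give 80% power for a difference of about 0.10. Separately, at the stated alpha the paragraph's two results do not appear to share one SD: 29 per arm goes with 0.12, and the control difference of 0.13 goes with about 0.13.

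This rests on a two-sided 5% t test, equal diet arms, 29 and 12 completers, and the pilot SDs taken at face value. The 0.133 needs no assumption about the pilot split; the ends of the 70-74% range do. Severity is should-fix: a stated property of the primary comparison is unsupported, but the shift is moderate and the correction leaves the design unchanged.

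**What to change.** Either of two corrections to the Sample size paragraph would do.

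1. Use one SD of about 0.13 for both comparisons and say that it comes from the feasibility SDs. Restate that 29 completers per diet arm give about 72-74% power for 0.09, or 80% power for about 0.10. Keep 0.13 as the detectable control difference and name the SD behind it.
2. Keep 0.12, state the evidence for it (for example the pilot arm sizes, if they yield that value), and correct the control figure to about 0.12.

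The cost is the rewording of one paragraph. Under the first option the stated power becomes less favourable. Neither option needs extra participants. Holding both 80% power and the 0.09 target at an SD of 0.130-0.133 would take 34-36 completers per diet arm, but that is a design choice which this correction does not require.

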**Methods and design:**

Eat Smart is a randomised controlled trial and aims to recruit 100 adolescents over a 2 1/2 year period. Families will be invited to participate following referral by their health professional who has recommended weight management. Participants will be overweight as defined by a body mass index (BMI) greater than the 90^th ^percentile, using CDC 2000 growth charts. An accredited 6-week psychological life skills program 'FRIENDS for Life', which is designed to provide behaviour change and coping skills will be undertaken prior to volunteers being randomised to group. The intervention arms include a structured reduced carbohydrate or a structured low fat dietary program based on an individualised energy prescription. The intervention will involve a series of dietetic appointments over 24 weeks. The control group will commence the dietary program of their choice after a 12 week period. Outcome measures will be assessed at baseline, week 12 and week 24. The primary outcome measure will be change in BMI z-score. A range of secondary outcome measures including body composition, lipid fractions, inflammatory markers, social and psychological measures will be measured.

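### Enrolling 35 per diet arm leaves 28 completers at the stated 20% dropout, one short of the 29 required; the effect is minor

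*Protocol article*

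**What the plan says.** All figures on this point are in the protocol article.

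- **Basis of the calculation (Sample size).** It rests on "the difference in change in BMI z-score between the low fat and reduced carbohydrate groups", which the plan calls its primary comparison.
- **Inputs (Sample size; Statistical Analysis Plan).** The target is a "clinically important difference in change of BMI z-score between the two intervention groups of 0.09", "assuming standard deviation of 0.12", "with α = 0.05 and power of 80"%. Tests are two-sided: "Statistical significance will be based on two-tailed tests, with p < 0.05 considered significant".
- **Completers required (Sample size).** "we require 29 individuals in each intervention group to complete the study".
- **Dropout (Sample size).** The planning assumption is 20%. Attrition of 17% in the feasibility study is given in parentheses beside it.
- **Enrolment per diet arm (Sample size).** "we will enrol 35 individuals in each of the diet intervention groups".
- **Control arm (Sample size).** 12 completers are wanted and 15 are to be enrolled, again at 20% dropout.
- **Overall aim (Abstract, Methods and design).** The trial "aims to recruit 100 adolescents over a 2 1/2 year period".

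**The concern.** The number to enrol should deliver the number of completers required once the assumed dropout is taken off. In the diet arms it does not: the requirement, the dropout rate and the enrolment figure stand together in the Sample size section, and any two of them contradict the third.

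The shortfall falls on the comparison that the plan names as primary, and 29 is the smallest number per arm that reaches 80% power under the t-test, so there is no slack. If dropout runs at the assumed rate, the trial ends slightly below its declared power, and anyone checking participant flow against the plan will find that the planned figures do not agree.

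A lesser matter is that the three arms sum to 85 while the abstract gives a recruitment aim of 100. A reader cannot tell from the text which stage of the trial the 100 refers to.

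**Working it through.** **Inputs.** From Sample size: difference 0.09, SD 0.12, α = 0.05, power 80%, dropout 20%, feasibility attrition 17%, 29 completers and 35 enrolled per diet arm, 12 completers and 15 enrolled in the control arm. From Statistical Analysis Plan: two-sided testing. From the Abstract: recruitment aim of 100.

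**Step 1: reproduce the 29.** Standardised difference = 0.09/0.12 = 0.75.

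- Two-sample t-test, two-sided α = 0.05, power 80%: n = 28.90 per arm, rounded up to **29**. This matches the plan.
- Normal approximation, n = 2 × [SD × (z for α/2 + z for power)/difference]²: n = 27.91, rounded up to 28. This does not match, so the t-test is the likely basis of the plan's figure.

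**Step 2: apply the stated dropout to the stated enrolment.** Completers = enrolled × (1 − dropout) = 35 × 0.8 = **28**, against 29 required.

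**Step 3: number needed at 20%.** Enrolled = completers/(1 − dropout) = 29/0.8 = 36.25, rounded up to **37**. Check: 37 × 0.8 = 29.6.

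**Step 4: where 35 could come from.**

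| Route | Result | Rounded up |
|---|---|---|
| 29 × 1.2 | 34.8 | 35 |
| 29/0.83 (17% attrition) | 34.94 | 35 |
| 29/0.8 (stated 20%) | 36.25 | 37 |

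Two routes give 35. Division by 0.8, the one that matches the stated dropout, does not.

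**Step 5: effect on power (difference 0.09, SD 0.12).**

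| Completers per arm | t-test | Normal approximation |
|---|---|---|
| 29 | 80.1% | 81.5% |
| 28 | 78.7% | 80.1% |

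The loss is 80.1 − 78.7 = 1.4 percentage points by the t-test.

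**Step 6: control arm.** 15 × 0.8 = 12, as required. If SD 0.12 also applies to this comparison (an assumption; the plan does not repeat the SD there), 12 controls against 28 in a diet arm can detect 0.119 at 80% power, against 0.118 with 29. Both are inside the stated 0.13, so the shortfall does not matter for the control comparison.

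**Step 7: totals.** As stated: 35 + 35 + 15 = 85. With 37 per diet arm: 37 + 37 + 15 = 89. Both are below 100.

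**The case against.** The strongest reply is that nothing of substance is lost. One completer per arm and 1.4 points of power are well within the uncertainty of any planning assumption. By the normal approximation 28 per arm already gives 80.1%. At the only attrition rate that this group has observed, 35 × 0.83 = 29.05, and the target is met. All of this stands as an argument about size. It does not make the stated figures agree: the plan adopts 20%, its 29 follows from the t-test and not from the normal approximation, and 35 at 20% is 28.

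Two stronger readings are tempting, and the article supports neither.

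*That the authors multiplied by 1.2, and used a different formula for the controls.* No formula is shown. Division by 0.83 gives 35 as well. The control figure cannot separate the methods, because 12/0.8 = 15 and 12 × 1.2 = 14.4 also rounds up to 15. The mismatch is certain; its cause is not.

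*That 85 and 100 are contradictory totals.* The abstract speaks of recruiting 100, whereas Sample size gives numbers to enrol in each group. The FRIENDS programme and then the psychological interview with Stage 2 exclusion come before randomisation, so more must be recruited than randomised. A loss of 15% at that stage would take 100 to exactly 85; that rate is an assumption, as the article gives none. The study flow figure, where such counts might stand, is not available in the text reviewed. Nor can one say that staff would not know when randomisation is complete, since a number is given for each arm.

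**Conclusion.** The point holds as a minor arithmetic error in a primary sample-size statement. At the plan's own 20% dropout, 35 enrolled per diet arm gives 28 completers instead of 29, and t-test power of 78.7% instead of 80.1%. The enrolment figure that matches the stated inputs is 37 per arm, four more participants in all (74 against 70 in the two diet arms).

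The power figures take the plan's difference of 0.09 and SD of 0.12 as given, assume a two-sided two-sample t-test on completers, and apply a flat 20% loss in each arm. They follow the plan's own completer basis and do not model the intention-to-treat analysis that returns non-completers to baseline. The design is not undermined. The relation of 85 to 100 is a request for clarification and not an error.

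**What to change.** Make the diet-arm figures in Sample size agree, in one of three ways:

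1. Keep 35 per diet arm and state the expected yield at 20% dropout as 28 completers, with about 79% power.
2. Keep 35 and state that it rests on the 17% feasibility attrition (35 × 0.83 = 29.05). The control arm still holds on that basis: 15 × 0.83 = 12.45.
3. Keep 20% and 29, and restate the diet arms as 37 each, for a total of 37 + 37 + 15 = 89.

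The first two cost a sentence. The third adds four participants. It stays below the announced 100, and if that number is counted before FRIENDS, it leaves room for 11 losses (11%) before randomisation, against 15 (15%) with the present arms.

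Separately, add a clause saying whether the 100 are adolescents recruited before FRIENDS and the Stage 2 exclusion or adolescents randomised. If the former, give the loss expected before randomisation.
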